## Methods/design

### Objectives

The primary objective of this study is to compare accuracy of implant positioning in CO UKA versus RO UKA. Accuracy of implant positioning will be assessed by measuring differences in the planned implant position on preoperative CT scan versus the achieved implant position on postoperative CT scan. The null hypothesis is that there is no difference in accuracy of implant positioning between CO UKA versus RO UKA.

The secondary objectives are to compare the following outcomes between the two treatment groups:
Limb alignmentSurgical efficiencyPostoperative functional rehabilitationFunctional outcomesQuality of lifeRange of motionMobilisation distanceResource use and cost effectivenessComplications

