All patients will undergo preoperative and postoperative CT scans of the knee joint using a standardised protocol within a dedicated research scanner in the study hospital. The CT scans will be uploaded in DICOM (Digital Imaging and Communication in Medicine) format and then loaded onto Mimics software (Materialise) to calculate the accuracy of implant positioning. Accuracy of implant positioning will be assessed by comparing differences in the target values in the preoperative plan to the achieved values in the postoperative scan. These outcomes will be used to calculate root mean square errors values for accuracy of femoral and tibial component positioning within the coronal, sagittal, and axial planes as described by Bell et al. [4]. The posterior condylar offset ratio (PCOR) and posterior tibial slope will be assessed using the methods described by Gaudiani et al. and Johal et al. respectively [13, 23].

The WOMAC, OKS, SF-12, EQ-5D, and KOOS are validated tools for the clinical assessment of patients after knee arthroplasty [11, 12, 17, 22, 39]. In addition, the observers will calculate the UCH knee score to assess overall, pain, function, and mobility [19]. This will help to overcome any potential ceiling effect with the OKS and WOMAC and facilitate further subgroup analysis in patients with high functional demands [19]. Each of these clinician- and patient-reported scores will be collected preoperatively at the time of consenting to the study and also postoperatively at 6 weeks, 6 months, 1 year, and 2 years after surgery.

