### Sample size

Using the study by Bell et al. assessing differences in accuracy of component positioning between conventional and robotic UKA, the mean difference in femoral sagittal component positioning was set at 2° and standard deviation assumed at 4° [4]. Using a two-tailed, two-sample *t* test with a power of 80% (1–β), significance level of 5%, and an effect size of 0.5, this study required 128 patients to detect this minimum difference between the two treatment groups. To account for 10% attrition in the sample size during follow-up, the sample size was set at 140 patients.

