### Statistical analysis

The analysis of the per-protocol population will be considered the primary analysis. The differences between the CO UKA and RO UKA groups will be analysed by calculating the difference from baseline, per patient, and a two-sided confidence interval for the difference between the changes from baseline values will be calculated. This confidence interval will cover the true difference in the percentage change from baseline with a probability of 95%. The following statistical methods will be employed to analyse the data: descriptive statistics, independent *t* test, paired *t* test, analysis of variance, Fisher’s exact test, chi-square test, and graphical displays. Assumptions of normality will be tested with the D’Agostino test. Assumptions of homogeneity of variance will be tested with Levene’s test. If the distributional assumptions are (severely) violated, non-parametric techniques, such as Mann-Whitney’s test, will be employed. In the event that RO UKA is converted to CO UKA intraoperatively, analysis will be performed using the intention-to-treat population and the treatment actually received by the patients. Intraoperative conversion from RO UKA to CO UKA will be documented and presented and published as part of the study. The Bonferroni correction will be used to determine the level of significance due to multiple comparisons of secondary outcomes. Statistical significance is set at a *p* value < 0.05 for all analyses, and all statistical analysis will be performed using SPSS software version 26 (SPSS Inc., Chicago, IL, USA).

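### No primary variable is designated among six component-by-plane errors, and the multiplicity correction is limited to secondary outcomes, so the primary claim can rest on any of six tests at 0.05

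*Protocol article*

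**What the plan says.** All references are to the protocol article.

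- **Objectives.** "The primary objective of this study is to compare accuracy of implant positioning in CO UKA versus RO UKA". There is one global null: "The null hypothesis is that there is no difference in accuracy of implant positioning between CO UKA versus RO UKA". Neither sentence mentions a component or a plane.
- **Outcomes.** Accuracy is to be expressed as "root mean square errors values for accuracy of femoral and tibial component positioning within the coronal, sagittal, and axial planes", from CT at 6 weeks. Two further measures follow with no tier given: "The posterior condylar offset ratio (PCOR) and posterior tibial slope will be assessed using the methods described by" cited methods.
- **Sample size.** The calculation uses one variable: "the mean difference in femoral sagittal component positioning was set at 2° and standard deviation assumed at 4" degrees. It assumes a single two-sided two-sample t test at 5% with 80% power, which gives 128 patients, raised to 140 for attrition. The section does not call this variable the primary outcome.
- **Statistical analysis.** "The Bonferroni correction will be used to determine the level of significance due to multiple comparisons of secondary outcomes". The next sentence sets significance at a p "value < 0.05 for all analyses".

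**The concern.** A global null measured by several variables needs a rule for what counts as rejecting it: one designated variable, a composite, a fixed order, or a correction across the set. The article gives none of these for the primary objective, and the one correction it does give is confined to the secondary outcomes. A significant difference in any one component and plane could therefore be reported as meeting the primary objective at 0.05.

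Two things are at stake. The false-positive rate for the trial's main claim would be well above the nominal 5%. The stated power would also describe only one of the comparisons on which the claim might rest. The radiological observers cannot be blinded, because the implants differ in design, so leaving the choice of plane open until results are known adds a selection risk that is easily avoided.

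**Working it through.** **Inputs.** Difference 2°, SD 4°, so d = 2/4 = 0.5; two-sided alpha 0.05; power 80%; 128 evaluable, 140 randomised, 10% attrition (Sample size). Allocation 1:1 (Abstract). Number of errors: 2 components × 3 planes = 6 (Outcomes). Correlation between the six test statistics is not given, so a range is assumed.

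**1. Reproducing the plan's figure.** Normal approximation: n per arm = 2 × (1.960 + 0.842)² × 4²/2² = 62.8, so 63 per arm (126). The exact noncentral t gives 63.77, so 64 per arm = 128, with power 80.1%. The stated 128 is confirmed, for one comparison at 0.05.

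**2. Family-wise error with six tests at unadjusted 0.05.** If independent: 1 − (1 − 0.05)⁶ = 1 − 0.735 = 26.5%. With equally correlated normal test statistics (simulation, 500,000 draws, two-sided critical value 1.96):

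| Assumed common correlation | Chance of at least one false positive |
|---|---|
| 0 | 26.5% |
| 0.3 | 24% |
| 0.5 | 21% |
| 0.7 | 16% |
| 0.9 | 11% |

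Even at 0.9 the rate is about twice the nominal level.

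**3. Power if all six were treated as co-equal and corrected.** Alpha per test = 0.05/6 = 0.0083. For d = 0.5:

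- 64 per arm (the stated 128): 56.0% per comparison.
- 63 per arm (140 × 0.9 = 126): 55.1%.
- 70 per arm (all 140 evaluable): 61.1%.
- Restoring 80% needs 99 per arm = 198 evaluable, or 198/0.9 = 220 randomised.

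**4. If femoral sagittal error is the single primary.** Alpha stays at 0.05, and 128 evaluable with 140 randomised stand as the plan has them. This is the only arrangement of the two that the existing sample size supports.

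**The case against.** The strongest reply is that the article never says six primary tests will be run. The Outcomes section lists what is measured. The only test tied to positioning accuracy is the single t test in the sample size calculation, and one may reasonably read femoral sagittal position as the intended primary. An analysis plan that is not shown might also set out a hierarchy. The first part stands: a reader might infer that six unadjusted primary tests are planned, and the document does not support that as a statement of intent. What it does support is that nothing prevents such testing. The objective is global, the powered variable is never designated, and the correction is expressly limited to secondary outcomes. Because the article fixes the scope of the correction, an analysis plan that corrected across the planes would be altering a stated rule, and one that named a primary would be adding what the protocol should already contain.

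Two further readings go too far:

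- A reader might infer that the closing 0.05 sentence contradicts the Bonferroni sentence. It can equally mean the overall level that Bonferroni divides, or the cut-off for adjusted p values. The wording is ambiguous, not a proven contradiction. The article states no number of secondary comparisons, so the size of any gap between the two thresholds cannot be derived from it.
- A reader might add the posterior condylar offset ratio and posterior tibial slope to the primary family. No tier is given for them, and slope may overlap with tibial sagittal error, so the count here stays at six.

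**Conclusion.** The point holds in this form: the primary objective has six candidate variables, no designated one, and no multiplicity control. Read as written, the family-wise error for the primary claim is 26.5% under independence, which is the highest value in the range examined, and about 11% at a common correlation of 0.9. The true figure depends on correlations that the article does not give. The stated 80% power is correct for one comparison at 0.05 and falls to about 55–56% per comparison if the six are corrected by Bonferroni.

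Confidence is high on the missing designation and on the limited scope of the correction. It is lower on the 0.05 sentence, which needs clarifying only. The matter should be settled before comparative CT results are seen, because it decides what counts as success on the main question.

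**What to change.** 1. By a dated amendment, name femoral sagittal positioning error on the 6-week CT as the single primary outcome, tested at two-sided 0.05. The article describes recruitment as running from November 2017 to April 2021 with unblinded radiological observers, so the amendment should state that the choice was made without sight of comparative CT data and rests on the existing sample size calculation.
2. Place the other five component-plane errors, with the posterior condylar offset ratio and posterior tibial slope, in the secondary family under the protocol's own Bonferroni rule. Holm's procedure is an option.
3. Reword the last sentence of the Statistical analysis section so that two-sided 0.05 applies to the primary outcome and is the family-wise level for the secondary outcomes.

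Cost: an amendment and its documentation. Sample size, imaging and data collection do not change. The downside is that a significant difference in another component or plane would no longer meet the primary objective. The alternative of keeping all six co-equal with a Bonferroni correction would need about 220 randomised patients for 80% power on each comparison.

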### Adverse events

Adverse events are defined as any untoward medical occurrence in a patient or study participant, which does not necessarily have a causal relationship with the procedure involved. A serious adverse event (SAE) is an adverse event that results in hospitalisation or prolongation of existing hospitalisation, persistent or significant disability or incapacity, life-threatening clinical sequelae, or death. All SAEs during the protocol treatment will be reported directly to the sponsor using the SAE web form. The chief investigator will also assess the SAE for severity, causality, seriousness, and expectedness using pre-existing criteria provided by the sponsor and inform the Data Safety Monitoring Board (DSMB) within 3 days of the initial observation of the event. The protocol treatment period is defined as the period from the day that the first study patient is recruited into the trial to the day that the final study patient has completed 2 years follow-up. The chief investigator will also inform the London-Bloomsbury Research Ethics Committee and local Health Research Authority within 3 days of the SAE taking place. Safety aspects of the study are closely monitored by the sponsor and DSMB using unblinded data for its judgement. In cases where the SAE arises due to a problem with the robotic device, Stryker Limited will also be notified within 2 days of the event taking place. The chief investigator will record the following: onset date, complete description of the event, severity, duration, action taken, and outcome for each SAE. The chief investigator will also provide regular updates of all SAEs to the London-Bloomsbury Research Ethics Committee, Local Health Research Authority, DSMB, and sponsor.

### Data management

On-site monitoring visits shall occur throughout the course of the clinical study by the chief investigator. The chief investigator shall permit and assist the sponsor (should they choose to monitor the study) to carry out verification of all study forms against data in the source documents, which shall occur as per the departmental policy for undertaking such activities. University College Hospital recognises that there is an obligation to archive study-related documents at the end of the study. The study master file will be archived at University College London in accordance with the University College Hospital Standard Operating Procedure for Archiving of Investigator Site File (ISF) and Pharmacy Site File (PSF). It will be archived for a minimum of 5 years from the study end and no longer than 30 years from the study end.

### End of protocol treatment

Reasons for going off study protocol include:
Completion of last follow-up visit 2 years after surgeryPatient non-compliance or withdrawal (the reason for discontinuation will be recorded in the case report form)Intercurrent death

All patients included into this study are free to withdraw from the study at any time without compromise to their future treatment. On withdrawal, patients will revert to the standard follow-up regimen for routine (non-study) UKA at the study site. The end of study form will be completed and the reason for withdrawal documented. This form will also be completed if the patient is lost to follow-up or dies during the course of the study. Data to the point of discontinuation will be used for analysis.

### Monitoring

The chief investigator will monitor the progress of the clinical study in the form of monthly research meetings for those involved in the trial. The chief investigator will be responsible for day to day monitoring and management of the study. The UCLH/UCL/Joint Research Office, on behalf of UCL as Sponsor, will monitor and conduct random audits on a selection of studies in its clinical research portfolio. Monitoring and auditing will be conducted in accordance with the Department of Health Research Governance Framework for Health & Social Care (April, 2005) and in accordance with the sponsor’s monitoring and audit policies and procedures. As per the protocol, the principal investigator will email the sponsor twice yearly with the following: delegation log, adverse event log, deviation log, and any annual progress reports sent to the Ethics committee.

### Peer review

The study protocol has undergone independent external peer review. The suggestions and recommendations for improvement to the study design were implemented. The reviewers, sponsor, and London-Bloomsbury Research Ethics Committee reviewed the revised protocol documents and confirmed that all queries and suggestions had been fully addressed.

## Discussion

Accuracy of component positioning and limb alignment are important prognostic variables that affect implant survival and time to revision surgery following UKA [5, 9, 38]. CO UKA is performed using manually positioned alignment guides, limited intraoperative data on knee kinematics, and handheld milling devices or sawblades for bone resection. However, these manual techniques are highly dependent on the skill and expertise of the operating surgeon. Surgeon-induced errors in implant positioning are the leading cause of premature implant failure and early revision surgery following UKA [29–32]. RO UKA uses a preoperative CT scan to create a virtual three-dimensional reconstruction of the patient’s osseous anatomy. The surgeon uses this virtual model to plan optimal bone coverage, implant positioning, and limb alignment. An intraoperative robotic arm then helps to execute this plan with a high-level of accuracy and reproducibility, and stereotactic boundaries limit bone resection to the predefined femoral and tibial haptic windows [4, 10, 26]. This prospective randomised controlled trial will include 140 patients with symptomatic medial compartment knee arthritis undergoing primary UKA. Following informed consent, patients will be randomised to CO UKA (control group) or RO UKA (investigation group) at a ratio of 1:1 using an online random number generator. Observers will review patients at regular intervals for 2 years after surgery to record predefined study outcomes pertaining to accuracy of implant positioning, limb alignment, postoperative rehabilitation, clinical progress, functional outcomes, cost-effectiveness, and complications. The following statistical methods will be employed to analyse the data: descriptive statistics, independent *t* test, paired *t* test, analysis of variance, Fisher’s exact test, chi-square test, and graphical displays. The findings of this study will provide an improved understanding of the differences in CO UKA versus RO UKA with respect to accuracy of implant positioning, limb alignment, patient satisfaction, functional outcomes, implant survivorship, cost-effectiveness, and complications.

## Trial status

Protocol: version 1.0; date 18 April 2017.

Patient recruitment date: 1 November 2017.

Estimated completion of recruitment date: 1 April 2021.

Estimated completion of final follow-up: 1 April 2023.

## Data Availability

The datasets used and/or analysed during the current study are available from the corresponding author on reasonable request.

## Abbreviations

CO UKA: Conventional jig-based unicompartmental knee arthroplasty
CT: Computerised tomography
DSMB: Data Safety Monitoring Board
EQ-5D: European Quality of Life questionnaire with 5 dimensions for adults
KOOS: Knee injury and osteoarthritis outcome score
OKS: Oxford knee Score
RO UKA: Robotic-arm assisted unicompartmental knee arthroplasty
SAE: Serious adverse event
SF-12: Short-form health survey of 12 items
UCH: University College Hospital knee functional score
WOMAC: Western Ontario and McMaster Universities Arthritis Index
